**Methods and analysis:**

The QM2-RC encompasses three interconnected projects (Project 1, 2, and 3) aimed at developing a quality management strategy and evaluating its impact on system performance across New York State. This report specifically focuses on Project 3, which involves a stepped-wedge trial with 35 clinics receiving a quality management intervention that includes performance coaching. This intervention will be compared to a treatment-as-usual (TAU) condition for clinics not participating in the trial. Administrative data will be utilized to monitor outcomes over four years. The coaching intervention, guided by the Integrated Promoting Action on Research Implementation in Health Services (i-PARIHS) model, emphasizes interpreting quality measures and applying insights to enhance care. Coaches will provide support on data utilization, patient-centered care, harm reduction strategies, and the use of patient monitoring tools. The trial aims to evaluate clinic staff and leadership attitudes, experiences, and behaviors through surveys, semi-structured interviews, and external facilitator notes. Primary clinic outcomes will be assessed through adverse events, decreased clinic rates of substance use related emergency department visits and hospitalizations as well as mortality among patients within the first 12 months after admission to treatment after adjusting for individual and community level characteristics. This study is being developed over a multi-year period and will be informed by a mixed-methods approach incorporating multiple data sources, qualitative interviews, patient and clinic surveys. The study is being conducted in partnership with New York State Office of Addiction Services and Supports (OASAS) and will be informed by input from patient, providers, health insurers, family members and local governing units.

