Before the trial begins, clinics receiving the QM2 intervention will be randomized into six cohorts of six-month long interventions over three years. Clinics are randomized to onset of intervention in one of six time periods over the three years of the intervention rollout (years 2–4 of the project) and tracked using administrative data. Administrative data will be used for all clinic clients during each of the seven six-month periods (n ≈ 350/clinic) will be drawn from administrative data. The first six-month period will be a baseline prior to any intervention. Six clinics will be assigned randomly to one of six time periods for onset of intervention. Using administrative data, we will track clients within each clinic over four years, including a pre-intervention six-month baseline period. During the same four-year period, clients in clinics not participating in the stepped-wedge trial will be tracked to better understand changes in outcomes under treatment as usual (TAU) and to compare the outcomes of those clinics with clinics receiving the quality management intervention. We anticipate a final study population of approximately 91,000 individuals per year who are receiving treatment from one of the 571 enrolled outpatient substance use treatment programs. Because this is a stepped-wedge trial, all clinics (and as a result all clients within the clinics) will eventually get the intervention, the randomization will have to do with when the clinic is randomized rather than being assigned to a control or intervention group. Fig 2 illustrates the structure of the stepped-wedge trial.

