### Data and analytic plans

#### Project 3: Stepped-wedge trial.

*Quantitative Methods:* We will utilize Generalized Linear Mixed Models (GLMMs), which are commonly applied in the analysis of stepped-wedge trial [106,107]. The models will be structured as follows:

$$F(\mu_{ijk})=\mu +\beta_{j}+{\delta X}_{ij}+\alpha_{i}+\phi_{ik},\;\alpha_{i}\sim N\left(\text{0},\tau_{\alpha }^{\text{2}}\right),\;\gamma_{ij}\sim N(\text{0},\tau_{\phi }^{\text{2}})$$

where $\beta_{j}$ represents a fixed effect for time, $X_{ij}$ is an indicator for intervention in clinic *i* at time *j* (coded 0 for the control condition, then 1 from the start of the intervention in the clinic until the end of the study), and δ denotes the intervention effect. The models include random effects to account for clustering at both the clinic and individual patient levels, which are assumed to follow a normal distribution with mean zero and variances $\tau_{\alpha }^{\text{2}}$ and $\tau_{\phi }^{\text{2}}$, respectively. We will estimate the intervention effect while controlling for secular trends and adjusting for clustering within clinics ($\alpha_{i}$) and individual ($\phi_{ik}$), using mixed effects modeling with a binary distribution and logit link function. The models will be fitted using the *glmmTMB* package in R software [108,109]. The primary outcome will be adverse events, and the fixed-effects coefficients for the intervention effect, exponentiated, will indicate the extent to which the intervention changes the rate of adverse events. An offset term can be included to capture client differences in time at risk due to timing of treatment entry.

TAU clinics will be included in the model with an indicator variable. A post-hoc test of the intervention effect coefficient will compare TAU and performance coaching, and a TAU-by-time interaction will assess time trends within the TAU group. The GLMM analysis will be expanded by adding the clinics not receiving the performance coaching intervention during the study period. For TAU clinics, the intervention indicator will be coded 0 in all periods. This provides an additional estimate of trends ($\beta_{j}$) in outcomes in a much larger sample of clinics. Because the fixed effect for time ($\beta_{j}$) is estimated, the intervention effect (δ) can be interpreted as the degree to which performance coaching results in a lower rate of adverse events than what would be expected due to time alone in the absence of intervention.

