If we observe significant treatment effects (e.g., reduced adverse events) from the performance coaching intervention, we will conduct follow-up analyses to strengthen causal inference. Drawing on methods from treatment mechanism research, we will test whether hypothesized mediators (e.g., person-centered care, retention in treatment) are associated with outcomes. We will also examine moderation by population characteristics and regional variation (e.g., gender, location), as well as provider-level differences in implementation. Lagged treatment effects will be assessed using interaction terms between treatment and time since intervention start by cohort. These exploratory analyses will inform interpretation and guide qualitative inquiry.

*Data and specification:*

We will join multiple administrative data sources from New York State for years 2021–2027 to form our analytical dataset. We will use Client Data System (CDS), Medicaid claims, and NYS vital statistics data to form the analytic dataset. The OASAS treatment registry (CDS) will provide extensive clinical data on clients at treatment admission and will include descriptions of providers through the provider data system (PDS). Medicaid will provide medical diagnoses, healthcare services, SUD treatment services, and medication utilization data. The New York State Vital Statistics will be received from the outpatient clinics in the form of all-cause mortality for clients participating in the trial. Additional OASAS data will provide operational and staffing information for each clinic. To date, 75% of clients in the OASAS registry have been linked to Medicaid claims data.

Quality measures from Project 1 will encompass patient, clinic, and organizational factors, including demographics, clinical complexity, substance use patterns, prior healthcare utilization, community access, substance use trends, resources, psychosocial interventions, clinic structure, staffing, and MOUD use and retention. Primary outcomes include adverse events, healthcare utilization, and mortality. Adverse events are defined as SUD-related hospitalizations or emergency department visits, including overdose, within 12 months of treatment entry. Healthcare utilization includes all-cause emergency department visits or hospitalizations within the same timeframe. Mortality will be assessed as all-cause mortality. Outcome variables will be risk-adjusted to account for client health status.

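### The client random intercept in the binary-logit model cannot be estimated for outcomes recorded once per client, and the article does not fix the record unit that decides which outcomes those are

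*Protocol article*

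**What the plan says.** In the protocol article, Data and analytic plans, Project 3 (Quantitative Methods), the model has fixed period effects, an intervention indicator with coefficient δ, a clinic intercept α_i and a client intercept φ_ik: "The models include random effects to account for clustering at both the clinic and individual patient levels". It is to be estimated "using mixed effects modeling with a binary distribution and logit link function", and "The models will be fitted using the *glmmTMB* package in R software". The exponentiated intervention coefficient is to be read as the size of the change in adverse events. The distribution line under the equation gives the variance τ_φ² to γ_ij, a clinic-by-period symbol that does not occur in the equation, and not to φ_ik.

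Under Data and specification there are three primary outcomes. "Adverse events are defined as SUD-related hospitalizations or emergency department visits, including overdose, within 12 months of treatment entry". Utilization uses the same window for all-cause visits and admissions. "Mortality will be assessed as all-cause mortality"; the Abstract limits it to the first year, "as well as mortality among patients within the first 12 months after admission to treatment".

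Other parts of the article work in half-years. Materials and methods says "Administrative data will be used for all clinic clients during each of the seven six-month periods (n ≈ 350/clinic", and "we will track clients within each clinic over four years, including a pre-intervention six-month baseline period". The power paragraph counts 350 clients per clinic per six-month period and gives events per six months, with a single ICC of 0.05 and no client-level correlation. The number of records per client is not stated.

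**The concern.** A client intercept in a logistic model is learned only from how alike several 0/1 values of the same client are. If each client supplies one value, the data carry no such information, because client variation and Bernoulli variation cannot be told apart. The conditional coefficient δ nevertheless depends on the client variance: the larger the assumed variance, the further exp(δ) moves from 1 for the same observed risks. The reported effect would then be set by where the optimiser stops, and the Wald standard error by a nearly flat likelihood.

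Read literally, the outcome definitions give one value per treatment entry, and death happens once. The design and power text reads as repeated half-year observation. Whether the stated model can be fitted depends on which reading applies, and the article supports both.

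**Working it through.** **1. The plan's power figure.** Inputs from the power paragraph: 35 clinics, 5 crossover points with 7 clinics each, 350 clients per clinic-period, ICC 0.05, rate 0.23, RR 0.93. The total 35 × 350 × 6 = 73,500 matches and implies six periods. The Hussey–Hughes variance with a clinic intercept only is

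Var(δ) = Iσ²(σ² + Tτ²) / {(IU − W)σ² + (U² + ITU − TW − IV)τ²}.

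- I = 35, T = 6, U = 105, W = 2,695, V = 385, so IU − W = 980 and the second bracket is 3,430.
- Total variance 0.23 × 0.77 = 0.1771; σ² = 0.95 × 0.1771/350 = 0.000481; τ² = 0.05 × 0.1771 = 0.008855.
- SE = 0.0054. For a decrease of 0.23 − 0.2139 = 0.0161, power = Φ(0.0161/0.0054077 − 1.96) = 84.5%.

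Across variants of the variance, power is 82.7–85.4% and the detectable RR at 80% power is 0.932–0.935. The stated 0.93 is reproduced to rounding, with no client term in the calculation.

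**2. One record per client: what the data can tell.** With one value, the likelihood involves only the marginal risk p = ∫ expit(η + s·z) φ(z) dz, where φ(z) is the standard normal density and s is the client SD. For each s, solve for η₀ at p = 0.23 and η₁ at p = 0.2139; then δ = η₁ − η₀.

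| Client SD s | η₀ | η₁ | δ | exp(δ) |
|---|---|---|---|---|
| 0 | −1.208 | −1.302 | −0.093 | 0.911 |
| 1 | −1.443 | −1.552 | −0.108 | 0.897 |
| 2 | −1.954 | −2.098 | −0.144 | 0.866 |
| 3 | −2.571 | −2.759 | −0.189 | 0.828 |
| 5 | −3.924 | −4.211 | −0.288 | 0.750 |

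Every row fits the same two risks exactly. The same data can be reported as a 9% or a 25% reduction in odds. No fitting approximation is involved. The equality is exact for two risks; with clinic and period terms added the variance is only practically unidentified, as step 3 shows.

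**3. Simulation in the stated design.** There were 150 trials per cell (Monte Carlo error about 3 points), with marginal rate 0.23 and RR 0.93. The clinic SD was √(0.05/0.95 × π²/3) = 0.416 on the logit scale. Clinics were fitted as fixed effects. The client SD and the records per client are assumptions, since the article gives neither. Each trial was fitted by Laplace (assumed to be the package's method; the code was not the package itself) and by 61-point Gauss–Hermite quadrature. A Wald result counts as significant only if the Hessian is valid. LRT is the likelihood-ratio test.

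With one record per client, the fitted SD ranged from 0 to about 77 whatever the truth, and Hessians were valid in 39–55% of fits. Wald tests were significant in 41–45% of trials (Laplace) and 7–12% (quadrature). The LRT kept 81–87%. Omitting the client term gave 77–87% over all cells, including those below.

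| Records | Client SD | Valid Hessian (Laplace) | Laplace Wald / LRT | Quadrature Wald | No client term |
|---|---|---|---|---|---|
| 2 | 0.5 | 100% | 85% / 85% | 85% | 85% |
| 2 | 1 | 100% | 84% / 84% | 83% | 86% |
| 2 | 2 | 66% | 55% / 71% | 79% | 77% |
| 2 | 3 | 1% | 1% / 16% | 91% | 80% |
| 2 | 4 | 2% | 1% / 27% | 95% | 84% |
| up to 3 | 0.5 | 100% | 82% / 82% | 82% | 82% |
| up to 3 | 1 | 100% | 83% / 83% | 83% | 84% |
| up to 3 | 2 | 100% | 89% / 89% | 89% | 77% |
| up to 3 | 3 | 3% | 1% / 33% | 94% | 80% |
| up to 3 | 4 | 3% | 3% / 36% | 97% | 81% |

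At SD 3–4 the Laplace runs often stopped with large gradients, so those cells show instability and not an exact power. With a true SD of 0, the estimate sits on the boundary and only 37–47% of Hessians are valid, but the LRT keeps 80–83%.

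**The case against.** The best defence is that the records are half-years. The article speaks of all clients in each six-month period, of tracking over four years, and of events per six months. A client intercept is then an ordinary choice, and longer stays or readmissions would add records. The simulations support this for moderate client variance: the SD is well estimated and power is intact. The article also names only adverse events when it describes this model, and does not say that the client term is kept for death. Approximation method, type of test and convergence fallback are matters that a condensed article commonly leaves to an analysis plan.

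Most of this stands. A reader might infer that every client has only one to three records and that the coaching test will therefore lose almost all its power. The documents do not support that. The number of records is nowhere given; one to three is only what a 12-month window cut into half-years would yield. Near-total loss of power appeared only with one record and a quadrature-based Wald test, or with Laplace fitting and a large client SD for which the article gives no value. In a smaller simulation without clinic effects, Laplace failed at client SD 2 (0 of 60 trials significant, against 72% for a robust marginal test), but that rested on an assumed mix of 60% of clients with one record and 40% with two. The article also does not commit to a Wald test, and in most of the failing fits the invalid Hessian would be visible to the analyst.

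The defence does not reach the one-record outcomes. The article itself puts the term in the model and defines mortality, and on the literal reading the 12-month indicators, so that the term has nothing to be estimated from. A likelihood-ratio test protects the p-value there, but not the reported exp(δ).

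**Conclusion.** The point holds in a limited form. For any outcome with one 0/1 record per client, the client variance is not usefully identified. The plan's own risks are compatible with exp(δ) anywhere from 0.91 to 0.75 over client SD 0 to 5, and Wald inference is unreliable. This applies to mortality, if the stated model is used for it, and to adverse events and utilization if each is analysed as a single 12-month indicator.

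If clients have repeated half-year records, the term is estimable at client SD 0.5–1, with power of 82–85%. Concern remains there only for a Laplace fit with few records and a large client SD: about 2 with two records, about 3 with up to three. These thresholds rest on assumed client SDs, assumed Laplace fitting and code other than the named package. Nor can it be inferred that the client term should go everywhere: with repeated records and SD 3–4, quadrature gave 91–97% power against 80–84% without the term.

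**What to change.** - State the record unit for each primary outcome, reconciling the 12-month window from treatment entry with the six-month analysis periods, and say how readmissions are counted.
- For every outcome with one record per client, omit φ_ik and keep the clinic and period terms.
- Where clients have repeated records, choose one of two routes in advance. Either keep φ_ik, check the fit against adaptive quadrature and base the test on the likelihood ratio; or omit φ_ik and use clinic-clustered robust standard errors with a small-sample correction for 35 clinics, which also cover repeated records because clients are nested in clinics.
- Correct the distribution line so that τ_φ² belongs to φ_ik and not to γ_ij.

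The cost is wording and a little more analysis work. Where the term is dropped, the client-specific interpretation of the odds ratio is lost. For one-record outcomes it could not be estimated anyway; for repeated records dropping the term is a genuine trade-off, since it may cost some power if clients differ strongly.

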*Statistical Analyses of the Proposed Stepped-Wedge Trial:* Analyses will begin with examination variable distributions, appropriate transformations, and patterns for, followed by formal imputation methods if needed [110–112]. We will use Generalized Linear Mixed Models (GLMM) for the stepped-wedge design [106].

*Power Analysis for Primary Outcome Statistical power:* Power estimation for specific outcomes was conducted using PASS 2022 software and Monte Carlo simulation [113]. Sample size and baseline rates (μ) were estimated using administrative data. For 80% power, α = 0.05, ICC = 0.05, and a 5-crossover-point stepped-wedge-RCT with 7 clinics starting at each point, power calculations indicate 80% power to detect a small decrease (RR = 0.93) in adverse events with 35 clinics and 350 clients per clinic per 6-month period (n ≈ 73,500 total observations). This corresponds to a decrease from 0.23 to 0.21 events per 6 months. In racial/ethnic subgroups (10% of clients, n ≈ 35 per site), power remains 80% to detect a modest decrease (OR=0.78), from 0.23 to 0.18.

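### The primary adverse-event outcome is described and powered as an event rate but modelled as any/none with a logit link; model, effect measure and power basis need to be aligned

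*Protocol article*

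**What the plan says.** All references are to the protocol article; no separate SAP is at hand.

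- **Model** (Project 3: Stepped-wedge trial, Quantitative Methods): the intervention effect is estimated "using mixed effects modeling with a binary distribution and logit link function", with random effects for clinic and client, fitted in glmmTMB.
- **Interpretation** (same paragraph): the exponentiated coefficient "will indicate the extent to which the intervention changes the rate of adverse events". It adds: "An offset term can be included to capture client differences in time at risk due to timing of treatment entry".
- **Aim** (Abstract, Methods and analysis): "decreased clinic rates of substance use related emergency department visits and hospitalizations".
- **Definition** (Data and specification): "Adverse events are defined as SUD-related hospitalizations or emergency department visits, including overdose, within 12 months of treatment entry". It says neither the number of events nor at least one event.
- **Power** (Power Analysis for Primary Outcome): the design has five crossover points with seven clinics each, an ICC of 0.05 and 350 clients in each clinic and half-year. The claim reads: "power calculations indicate 80% power to detect a small decrease (RR = 0.93) in adverse events with 35 clinics". The same effect is then given in absolute terms: "This corresponds to a decrease from 0.23 to 0.21 events per 6 months".

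**The concern.** Most of the text describes events per unit of time: clinic rates, a change in rate, a time-at-risk offset, a rate ratio and events per 6 months. One client can have several emergency visits or admissions. The model that is fixed lets each record contribute only 0 or 1.

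Three things follow. The exponentiated coefficient is an odds ratio for any event, not a rate ratio. A log-time offset under a logit link multiplies the odds, not an event rate. And a fall in repeat events within a record, among clients who still have at least one, cannot show. At stake are whether the reported effect is the planned one and whether the stated 80% power belongs to the analysis that will be run.

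**Working it through.** **Inputs from the protocol.** 35 clinics in 5 sequences of 7; 350 clients per clinic-period; 73,500 observations, hence 73,500/(35 × 350) = 6 periods; ICC 0.05; α = 0.05 (two-sided assumed); baseline 0.23; RR 0.93, so 0.23 × 0.93 = 0.2139, a difference of 0.0161.

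**Assumptions.** Clinic random intercept and fixed period effects only, with no client random effect. The protocol gives no dispersion, so a range is shown.

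**Variance formula.** With X the 0/1 treatment indicator over 35 × 6 cells, the sum of squares left after removing clinic and period means is 105 − 64.17 − 77 + 52.5 = 16.33. The effect variance is therefore about 1/16.33 = 0.0612 times the cell variance. With the random intercept at the stated ICC the factor is 0.0608. Power = Φ(effect/SE − 1.96).

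**Step 1: the plan's own figure.**
- 0.23 as a proportion: total variance 0.23 × 0.77 = 0.1771; cell variance 0.1771 × 0.95/350 = 0.000481; SE = √(0.0608 × 0.000481) = 0.00541; power = Φ(0.0161/0.00541 − 1.96) = 84.5%.
- 0.23 as a Poisson mean: total variance 0.23; SE = 0.00616; power = 74.3%.

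Other variance conventions give 82.7 to 85.4% and 72 to 76%. The RR that gives exactly 80% is 0.932 to 0.935 on the binary reading and 0.923 to 0.926 on the Poisson reading. Either is close to 0.93, so the stated 80% does not show which outcome type was powered. The subgroup line does not settle it: 0.23 to 0.18 is a ratio of 0.78, but the protocol labels 0.78 an odds ratio, and the odds ratio is (0.18/0.82)/(0.23/0.77) = 0.73.

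**Step 2: any/none against count, if 0.23 is events per client and each client's rate is multiplied by 0.93.** P(any) = 1 − exp(−L) for Poisson, or 1 − (1 + kL)^(−1/k) for negative binomial with dispersion k. Work is on the log scale: cell variance = Var/(mean² × 350), averaged over the two arms; between-clinic variance 0.05 × 0.77/0.23 = 0.167. The count effect is −ln 0.93 = 0.0726 throughout.

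| k | P(any), control to intervention | Any/none effect / SE | Any/none power | Count effect / SE | Count power |
|---|---|---|---|---|---|
| 0 (Poisson) | 0.2055 to 0.1926 | 0.0648 / 0.0264 | 69% | 0.0726 / 0.0280 | 74% |
| 1 | 0.1870 to 0.1762 | 0.0594 / 0.0280 | 57% | 0.0726 / 0.0309 | 65% |
| 2 | 0.1724 to 0.1631 | 0.0553 / 0.0293 | 47% | 0.0726 / 0.0335 | 58% |

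A 600-run simulation of grouped logistic and quasi-Poisson fits gave 68% against 70% (k = 0), 55% against 64% (k = 1) and 40% against 54% (k = 3).

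**Step 3: a different effect pattern.** Let coaching cut the chance of any event by 7% and leave the number of events among affected clients unchanged. At mean 0.23, any/none against count power is then about 78% against 73% (Poisson), 73% against 65% (k = 1) and 69% against 57% (k = 2). The ordering reverses.

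**Step 4: a heavy tail.** With client rates lognormal (SD 1.5 on the log scale) and a proportional effect, the plain count reaches 34% and any/none 39%.

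**The case against.** The strongest reply is that no count is being dichotomised. The definition says neither number of events nor any event; the binary distribution is the only explicit statement of outcome type; clinic rates can mean the proportion of clients with an event; and reading 0.23 as a proportion gives about 84%, in line with plan. On the count reading even a Poisson count reaches only about 74%, so much of the gap to 80% is not due to any/none. The client random effect suggests repeated records per client, so events in different 6-month periods would be kept if records are per period. The article gives both a 6-month and a 12-month window, which leaves the record unit open.

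All of this stands, and it limits the size of the point. A reader might infer that the endpoint is a count and that any/none analysis costs a fixed 4 to 15 points of power. The document does not support that: it defines no count, gives no dispersion, and does not say whether coaching would act on first or repeat events, which decides the sign (step 3).

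The label alone also changes little numerically. The odds ratio for any event implied by step 2 is (0.1926/0.8074)/(0.2055/0.7945) = 0.92 under Poisson, and 0.93 and 0.94 at k = 1 and 2, before any client random effect.

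None of this removes the mismatch. If a rate is meant, the model does not fit it. If any/none is meant, the abstract, the reading of the coefficient and the power statement do not fit the model.

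**Conclusion.** The inconsistency is established from the text: a rate-type aim, interpretation and power basis stand beside a binary logit model. The power consequence is conditional. With 0.23 as events per client and a proportional 7% fall in each client's rate, any/none power is about 69%, 57% and 47% at dispersion 0, 1 and 2, against the stated 80% and against 74%, 65% and 58% for the count. With 0.23 as a proportion there is no shortfall against plan. If coaching lowers only the chance of any event, the binary model is the more powerful. The claim is therefore that the outcome type must be settled and the power recomputed, not that a known amount of power is lost. It should be corrected before analysis; confidence is medium.

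**What to change.** State whether the primary outcome is the number of events or at least one event, then align the text.

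- **If a rate is intended, as most of the text says:** in Quantitative Methods, make the primary model a log-link negative binomial GLMM on the number of SUD-related emergency visits and hospitalizations, with log time at risk as offset, reported as a rate ratio. The already named glmmTMB fits it. Keep the any/none logit model as a sensitivity analysis. Handle very frequent users through the dispersion model or a pre-specified truncated-count sensitivity analysis. A capped count should not be primary: it is not negative binomial, and its mean does not scale with time at risk.
- **If any/none is intended:** restate the abstract, the reading of the coefficient and the power statement as the proportion with at least one event and an odds ratio, and remove the rate wording.

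Either way, recompute the power for the model used and, for a count, state the assumed dispersion. The cost is wording and one power re-run, with no new data, clinics or clients. The downside of the count route is that overdispersion must be modelled, and a heavy tail can reduce precision.

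### The primary model yields an odds ratio that the plan reads as a change in the event rate; power is on the rate-ratio scale, and the subgroup effect labelled OR = 0.78 is in fact a risk or rate ratio of 0.78

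*Protocol article*

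**What the plan says.** All statements are in the protocol article, Data and analytic plans, Project 3: Stepped-wedge trial.

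- **Model (Quantitative Methods).** The intervention effect is estimated with random effects for clinic and for individual, "using mixed effects modeling with a binary distribution and logit link function".
- **Interpretation (same place).** The fixed-effect coefficient, "exponentiated, will indicate the extent to which the intervention changes the rate of adverse events". The next paragraph reads δ again as "the degree to which performance coaching results in a lower rate of adverse events" than time alone would produce.
- **Time at risk (same place).** "An offset term can be included to capture client differences in time at risk due to timing of treatment entry". The form of the offset is not given.
- **Main power (Power Analysis for Primary Outcome).** "For 80% power, α = 0.05, ICC = 0.05", with "a 5-crossover-point stepped-wedge-RCT with 7 clinics starting at each point". The detectable effect is RR = 0.93, described as 0.23 falling to 0.21 events per 6 months, with 350 clients per clinic per period and about 73,500 observations.
- **Subgroup power (same place).** With about 35 clients per site, "power remains 80% to detect a modest decrease (OR=0.78), from 0.23 to 0.18".

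**The concern.** Three scales are used as if they were interchangeable: an odds ratio from the fitted model, a rate change in its interpretation and a rate ratio in the main power statement. At a baseline of 0.23 the event is not rare, so an odds ratio lies visibly further from 1 than the corresponding risk or rate ratio. If the exponentiated coefficient is published as the plan describes it, the size of the benefit will be overstated.

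The offset adds to this. A log-time offset gives a rate under a log link, or under a complementary log-log link for binary data. Under a logit link it does neither.

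The subgroup line then attaches an odds-ratio label to a pair of rates that do not have that odds ratio. This leaves the target effect for the racial/ethnic analyses ambiguous, in a study motivated by disparities.

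**Working it through.** **Inputs from the protocol article.** Baseline 0.23; main RR 0.93 (0.23 to 0.21); subgroup 0.23 to 0.18, labelled OR = 0.78; 5 crossover points × 7 clinics = 35 clinics; 350 clients per clinic-period (35 in the subgroup); ICC 0.05; α 0.05. Six periods are implied, since 35 × 350 × 6 = 73,500.

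**Assumptions.** Two-sided α; exchangeable within-clinic correlation; no added within-person correlation; 0.23 treated as a proportion wherever odds are computed.

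**Step 1. Reproduce the stated power.** The Hussey–Hughes variance of the intervention effect is

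Var = Iσ²(σ² + Tτ²) / [(IU − W)σ² + (U² + ITU − TW − IV)τ²],

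with I = 35, T = 6, U = 7 × 15 = 105, W = 49 × 55 = 2695 and V = 7 × 55 = 385. Hence IU − W = 980 and the τ² multiplier is 11025 + 22050 − 16170 − 13475 = 3430.

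*Subgroup, 0.23 to 0.18, Poisson variance.*
- Total variance (0.23 + 0.18)/2 = 0.205.
- τ² = 0.05 × 0.205 = 0.01025; σ² = 0.95 × 0.205/35 = 0.005564.
- Var = 35 × 0.005564 × 0.06706 / (980 × 0.005564 + 3430 × 0.01025) = 0.01306/40.61 = 0.0003216, so SE = 0.01793.
- Power = Φ(0.05/0.01793 − 1.96) = Φ(0.828) = **79.6%**, which matches the stated 80%.

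*Main effect.* The same method reaches 80% power at 0.213 (RR 0.926), and in the subgroup at 0.180 (RR 0.782). These round to the stated 0.93 with 0.21, and 0.78 with 0.18. At exactly RR 0.93 (0.2139) main power is 75.8%; the rounding of 0.926 to 0.93 explains the gap. With binomial variance the results are 85% (main, RR 0.93) and 88% (subgroup, 0.18), further from the stated 80%. The power therefore looks like a rate-ratio calculation.

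**Step 2. Check the subgroup label.**
- RR = 0.18/0.23 = 0.783.
- OR = (0.18/0.82)/(0.23/0.77) = 0.735.
- OR 0.78 from 0.23: odds 0.78 × 0.2987 = 0.233, so p = 0.233/1.233 = 0.189, not 0.18.
- Rounding: with the baseline at 0.23, values from 0.175 to 0.185 give OR 0.710 to 0.760, which excludes 0.78. Only the extreme corner 0.225 to 0.185 reaches 0.782.
- Power if OR 0.78 were literal (0.23 to 0.189): Φ(0.0410/0.01813 − 1.96) = 62% with Poisson variance, 72% with binomial.

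**Step 3. What the logit coefficient shows when the true ratio is 0.93.** RR 0.93 takes 0.23 to 0.2139. The marginal OR is (0.2139/0.7861)/(0.23/0.77) = 0.911. With a normal patient effect of SD s, find the intercepts that give marginal risks 0.23 and 0.2139, and take the exponentiated difference. The protocol gives no value for s, so a range is shown.

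| Assumed patient SD | exp(δ) | Read as a reduction of |
|---|---|---|
| 0 | 0.911 | 9% |
| 1 | 0.897 | 10% |
| 1.5 | 0.883 | 12% |
| 2 | 0.866 | 13% |
| 2.5 | 0.847 | 15% |

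The true reduction is 7% in every row.

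**Step 4. The offset, if entered as log time.** Under logit the odds scale with time. A constant hazard gives 1 − 0.77^(t/6), with t in months.

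| Time at risk | Logit + log time | Constant hazard |
|---|---|---|
| 3 months | 0.130 | 0.123 |
| 6 months (anchor) | 0.230 | 0.230 |
| 12 months | 0.374 | 0.407 |

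With or without the offset, exp(δ) remains an odds ratio.

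**The case against.** The best defence is that this is loose wording in an article that condenses a fuller plan. Rate is often used informally for a proportion, and the text never calls exp(δ) a rate ratio. The offset is optional and its form is unstated, so log time is this review's assumption; such detail normally sits in an analysis plan. A conditional odds ratio is a legitimate estimand, and the upper part of the 9–15% range depends on assumed patient SDs. With no patient effect the gap is only 0.93 against 0.911. Near the six-month anchor the offset error is small: 0.007 at 3 months.

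Most of this stands as a limit on size. It does not remove the contradiction, because the article itself fixes the link, states the interpretation twice and powers on another scale.

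Two stronger readings are tempting and not supported. A reader might infer that the subgroup power is wrong. It is not: 80% is reproduced for the stated rates on the rate scale, and it fails only if OR = 0.78 is taken literally. A reader might also infer that the trial's effects are wrong or its primary test invalid. Nothing has been reported yet, and δ = 0 is the same null hypothesis under either name.

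**Conclusion.** The concern holds as a mismatch of scales on the primary outcome. As written, the logit model gives a conditional odds ratio that the plan would present as a rate change. A true 7% reduction would read as about 9% with no patient effect, and as 10–15% for assumed patient SDs of 1 to 2.5. The direction needs no assumption about the SD: for a protective effect at this baseline, the odds ratio is further from 1 than the risk ratio. The offset point is conditional on its being used and entered as log time.

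The subgroup label is wrong almost regardless of rounding: the stated rates give RR 0.78 and OR 0.73. The stated 80% stands for those rates, given six periods, exchangeable correlation, two-sided α and Poisson variance. What is at stake is the size of the reported effect and the clarity of the subgroup target, not the validity of the test.

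**What to change.** Choose one scale and use it in the model, the interpretation and the power statement.

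- **Option A, rate scale.** Model event counts per client-period with a log link (Poisson or negative binomial, both in glmmTMB) and log person-time at risk as offset. Then exp(δ) is the rate ratio on which power was set, and with normal random intercepts it is the same conditionally and marginally. The cost is a change of family and link, and a statement that the outcome is the number of events rather than any event, which the outcome definition does not settle.
- **Option B, binary scale.** Keep any-event as the outcome, with a complementary log-log link and the log-time offset, or with logit and no offset. Call exp(δ) what it is (a hazard ratio under complementary log-log, an odds ratio under logit, each conditional on the random effects). Report a standardised risk ratio and risk difference beside it, and restate power on the matching scale. The cost is one standardisation step and revised power wording.

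In either case relabel the subgroup effect as RR = 0.78 (OR about 0.73) for 0.23 to 0.18; the 80% can then stay on the rate scale. If an odds ratio of 0.78 was really intended, change the second rate to 0.19 and restate the power, which would be about 62–72%. Make the change before outcome data are analysed.
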